LivR Well is a multidisciplinary intervention aimed at reducing mortality and readmission through a home-based, liver optimisation programme. A prospective, single-arm feasibility study was conducted from March to October 2021 and enrolled 32 patients with ACLF (manuscript in progress). Participants received weekly medical review, nursing support, oral nutritional supplementation and consultation by dietetics, physiotherapy, pharmacy, social work and neuropsychiatry. The primary outcome was safety. Secondary outcomes were attrition, disease severity, healthcare utilisation, and patient-reported outcomes. Participants had a baseline median Charlson Co-Morbidity Index of 4 (IQR 3–5.5) and Model for End-Stage Liver Disease (MELD) score of16.5 (IQR 13–20.5). Handgrip strength in 11/23 (48%) met sex-specific sarcopenia criteria. Three patients died at 16, 148, and 197 days from enrolment. The 28-day mortality was 3% and the 30-day readmission rate was 18.75%. Median MELD score improved to 15 at 28 days (*p* = 0.16). The Chronic Liver Disease Questionnaire showed improvement in ‘fatigue’ (*p* = 0.02) and ‘worry’ (*p* = 0.03), at week 6. Patients, carers, and clinicians reported a positive experience in 100% and generated themes of acceptability, health literacy and insight, and autonomy. LivR Well cost $4947 AUD compared to $16,197 AUD for ACLF hospitalisation [3]. These results indicated that LivR Well was safe and acceptable, and likely to reduce both mortality and costs.

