#### Screening and randomisation

Patients will be screened against inclusion and exclusion criteria at the time of diagnosis of ACLF or hepatic decompensation. Those who meet the criteria will be enrolled into the study and provided informed consent. These recruited patients will be randomised in a 1:1 ratio to either the LivR Well programme or to complex care liver clinic in the control arm. Participants will be computer randomised and informed of their allocation by the CLD nurse specialist prior to discharge or within 24 hours of obtaining informed consent. Patients from both study arms will be registered on the Virtual Hospital masterlog through the Microsoft Power Apps program. Due to the nature of the intervention, blinding of study participants or clinical staff administering the LivR Well programme will not be possible. However, outcome ascertainment for the primary outcome, as well as the health services utilisation secondary outcomes will be blinded. Furthermore, all data analyses will be undertaken in a blinded manner. The statistician will be blinded to the feasibility study data results and the treatment allocation of the RCT.

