#### Interim analysis

A data monitoring committee will consist of 3 senior independent clinician researchers without competing interests. An interim analysis will be conducted and we will adopt a Bayesian approach for an adaptive trial design where efficacy and futility criteria will be based on the probability of treatment effects, given the observed data in our feasibility study. One interim analysis will be performed in the ACLF and decompensated cohort when 50% of patients have been randomised and have completed 12 weeks of follow-up. We will stop the RCT for efficacy if the posterior probability (Pr) that the hazard ratio (HR) is < 1 is > 90% (Pr (HR <1|data) > 0.9. Similarly, we would stop for futility if Pr (HR <1|data) < 0.1. The results are reviewed by the independent data monitoring committee who will ultimately guide the decision to continue or cease the study.

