#### Sample size

Sample size calculations were performed for each of the ACLF and hepatic decompensation arms using a 2-sided alpha of 5%, a power of 80%, and an anticipated 20% dropout.

For the ACLF cohort, we used the primary endpoint 28-day mortality, based on published rates of 22–74%, with a rate of 33.9% demonstrated in a study of 1343 hospitalised patients at 29 liver units in 8 European countries [2]. A 75% reduction in mortality in the intervention group generates a mortality rate of 8.5%, a conservative estimate considering our feasibility study of 59 participants resulted in a 3% 28-day mortality rate. We calculate a total sample size of 120 participants or 60 in each arm for the ACLF cohort. For the hepatic decompensation cohort, the sample size calculation is based on the primary endpoint of 30-day re-admission, which is estimated 17–38% [3, 29, 30]. Re-admission rates in our feasibility were 50% lower than anticipated at 18% by 30-days therefore we used an anticipated 17% 30-day re-admission rate in the intervention arm. We calculate a total sample size of 320 or 160 in each arm for the hepatic decompensation cohort. . Sample size calculation was performed using Stata statistical software, version 16.1 for Mac (StataCorp, College Station, TX, USA).

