#### Statistical analyses

The data analysis for the primary composite endpoint of death, referral for liver transplantation or 30-day readmission from the date of hospital discharge will be undertaken on an intention-to-treat basis. A 28-day mortality rate will be calculated from the date of randomisation. For the primary and other binary outcomes, chi-squared tests will be used to compare the intervention and control groups. Survival analyses will also be undertaken, with the generation of Kaplan-Meier curves and Cox regression analyses to derive (adjusted) hazard ratios. For continuous outcomes, t-tests or non-parametric equivalents (e.g., Mann-Whitney tests) will be applied to compare the intervention and comparator groups. A *p* value of 0.05 is considered significant and 95% confidence intervals will be reported for all effect estimates Three exploratory subgroup analyses are planned: (a) comparing groups by the source of referral—conducted to address bias created following randomisation whereby in-patients in the intervention arm may be discharged home earlier due to perceived safety with regular home visits compared to those in the control arm. This subgroup analysis will account for differences between those admitted from in-patient admission compared to the emergency department or the ambulatory liver clinic; (b) comparing groups by re-enrolment to LivR Well after drop out due to unplanned re-admission to hospital. Data from the first enrolment to LivR Well will be included in the primary outcomes on an intention-to-treat basis and (c) patients with COVID-19 at the time of referral. Analyses will be performed using Stata statistical software, version 16.1 for Mac (StataCorp, College Station, TX, USA).

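### The interim efficacy limit of Pr(HR<1) > 0.90, with p = 0.05 kept at the end, does not fit the stated two-sided 5% alpha and 80% power

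*Protocol article*

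**What the plan says.** Protocol article, Interim analysis: one look in each cohort, "when 50% of patients have been randomised and have completed 12 weeks of follow-up". The efficacy rule is "We will stop the RCT for efficacy if the posterior probability (Pr) that the hazard ratio (HR) is < 1 is > 90" per cent. The futility rule is "Similarly, we would stop for futility if Pr (HR <1|data) < 0.1". The criteria rest on the probability of treatment effects, "given the observed data in our feasibility study". An independent committee reviews the results and guides the decision to continue or cease.

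Sample size: both cohorts were sized "using a 2-sided alpha of 5%, a power of 80%, and an anticipated 20% dropout".

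Statistical analyses: chi-squared tests for the primary and other binary outcomes, with Cox models alongside; a p "value of 0.05 is considered significant". No allowance for the interim look is stated.

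Background: "A prospective, single-arm feasibility study was conducted from March to October 2021 and enrolled 32 patients with ACLF". It used the APASL definition of ACLF, whereas the RCT uses the EF-CLIF criteria. Sample size gives the size of the same study as 59.

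**The concern.** A posterior limit of 0.90 is loose for an efficacy stop halfway through a trial that claims 5% two-sided error. The interim look alone can spend four times the 2.5% available in the direction of benefit, so no choice of final significance level can recover it. The thresholds themselves conflict with the stated alpha, so this is not detail waiting for an analysis plan.

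At stake is an early stop with about 60 ACLF patients or 160 decompensation patients. That could either support wider adoption of an ineffective programme or leave an effective one with an inconclusive result. Neither can be undone once randomisation has ended.

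**Working it through.** **The design's own figure.** For 33.9% against 8.5%, two-sided 5%, 80% power and continuity correction, n is 47 per arm, 94 in total; 94/0.80 = 118, against the stated 120. The ACLF size therefore does rest on a two-sided 5% alpha. For decompensation no single control rate is given; an assumed 32% against 17%, without continuity correction, gives 256/0.80 = 320.

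**Model.** Z1 (interim) and Z2 (final) are bivariate normal with correlation √0.5 = 0.707. With a flat prior, Pr(HR<1) > 0.90 means Z1 > 1.2816, and Pr < 0.10 means Z1 < −1.2816. Final success is Z2 > 1.96. Under the planned effect at nominal 80% power, Z2 has mean 1.960 + 0.842 = 2.802 and Z1 has mean 2.802 × 0.707 = 1.981.

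**Reading A: crossing the limit counts as efficacy.**
- No effect: interim 10.0% + final 0.8% = 10.8%, against 2.5%.
- It is also 10.8% if the futility limit is ignored, 11.0% with the look at 40% information and 10.6% at 60%.
- Binomial simulation (Beta(1,1) priors, chi-squared final test): 11.4% for ACLF at a common rate of 33.9%, and 10.5% to 11.2% for decompensation.

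**Reading B: a stopped cohort is still tested at p = 0.05.**
- No effect: 2.5% at the interim (Z1 > 1.96) + 0.8% at the end = 3.3%.
- Planned effect: 75.8% of trials cross 1.2816 but only 50.8% exceed 1.96, so 75.8 − 50.8 = about 25% stop early with p > 0.05. Power is 50.8 + 11.4 (from trials that continue) = about 62%.

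**Futility limit.** Under no effect it fires with probability Φ(−1.2816) = 10%. With a flat prior, Z2 given z1 is normal with mean √2·z1 and variance 1. At an observed HR of 1 (z1 = 0), the predictive chance of final success is 1 − Φ(1.96) = 2.5%, yet the trial continues.

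**If feasibility data enter the posterior.** The text gives no prior or weight, so these are assumptions, all computed under no effect.
- ACLF, normal prior on log HR: 1/32 deaths against 33.9% gives HR = ln(1 − 0.03125)/ln(1 − 0.339) = 0.077, log HR −2.57, variance 1. Interim deaths are 60 × 0.339 = 20.3, so the precision of the trial estimate is 20.3/4 = 5.09. The rule stops if −2.57 + 5.09x < −1.2816 × √6.09, that is x < −0.116. With SE 0.443 the probability is about 40%. A slightly larger prior variance (1.092) gives 36%.
- ACLF, pooling into the intervention arm, control rate 33.9%: about 67% with 1/32 and 88% with an assumed 2/59.
- Decompensation, pooling 6/32: 8.2% at a control rate of 17%, 10.0% at 20%, 23% at 32% and 31% at 38%. Pooling an assumed 11/59: 7.4% at 17%, 34% at 32% and 49% at 38%. Without pooling, the figures at 17% and 20% are 10.6% and 10.5%.
- Decompensation, normal prior: 21% to 41% at control rates of 32% to 38%.

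**The case against.** The strongest reply is that the protocol says only that the trial would stop, not that crossing declares efficacy, and that the named inferential test is chi-squared at 0.05. The committee guides the decision and is not bound by the limit. This stands in part: 10.8% is conditional on the rule being followed and crossing being read as efficacy. It does not rescue the plan, because Reading B still exceeds 2.5% and loses about 18 points of power. Committee discretion does not recalibrate a limit that is too loose.

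Stronger readings are tempting but not supported:
- **One error rate of about 40% with feasibility data.** This comes from one choice of prior, control rate and event count. The phrase about the feasibility study may also mean only that it motivated the criteria.
- **The rule cannot be run.** The article says "The statistician will be blinded to the feasibility study data results and the treatment allocation of the RCT". That sits awkwardly with using those results in a posterior, but another analyst could supply the prior.
- **The hazard ratio is a 12-week quantity.** Twelve weeks of follow-up triggers the look; the text does not say which events form the HR.
- **Crossing in one cohort stops everything.** The Design section calls the two populations independent, so stopping by cohort is a natural reading.
- **A 20% error across both cohorts.** The arithmetic, 1 − (1 − 0.108)², is right for independent cohorts, but they have separate primary outcomes and the protocol claims no joint control.

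The prior's form and simulated operating characteristics may properly sit in an analysis plan that is not shown. The criticism is of the stated thresholds only.

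**Conclusion.** The point holds and should be fixed before the interim look. The 0.90 limit, the unadjusted final p of 0.05 and the stated 5% alpha with 80% power cannot all stand. The flat-prior figures above also take nominal 80% power and half the information at the look.

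Borrowing from the feasibility study, which has no control arm, a different ACLF definition and two stated sizes, would generally raise the error. Under the constructions tried the range is roughly 36% to 88% for ACLF (at the 33.9% control rate) and 8% to 49% for decompensation. There is no increase at readmission control rates of 17% to 20% when n = 32. These ranges show how far the answer depends on what is unstated; they are not estimates of the trial's error rate. The futility limit detects probable harm and would seldom stop an ineffective programme.

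**What to change.** For each cohort, state a neutral or vague prior that excludes the feasibility data, and say that crossing a limit applies to that cohort.

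- **Efficacy:** calibrate the limit to the stated alpha. One example is an O'Brien-Fleming type boundary: Pr > 0.997 at the interim (z about 2.77, two-sided p about 0.0056) with final p < 0.048. This gives about 2.5% one-sided error. Other calibrated pairs would serve: about 0.9985 at the interim with p = 0.05 kept at the end gives 2.55%.
- **Futility:** replace the 0.1 limit with a non-binding rule on the predictive probability of final success, for example below 10%. That is z1 < (1.979 − 1.282)/√2 = 0.49, which stops about 69% of trials under no effect and about 7% under the planned effect.

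The cost is protocol wording and a short simulation. Power is about 79.7% with the efficacy boundary alone, and about 78% if the futility rule is also followed. The real price is fewer early efficacy stops: under the planned effect they fall from about 76% to about 21%.

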#### Design

The RCT will be a multi-site, non-blinded, parallel-group study with two independent population arms to determine the efficacy and safety of the new model of care (LivR Well) compared to standard care and to inform a cost-effectiveness analysis.

This study protocol was developed in line with Recommendations for Interventional Trials (SPIRIT) guidelines including the SPIRIT checklist [17], which has been adapted in accordance with World Health Organisation registration (Appendix 1) and the CONSORT extension to pilot and feasibility trials [18] (Table 3, Appendix 2).

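### Both interim criteria rest on favourable single-arm feasibility data, which weakens the only numeric bound pointing towards harm by an amount that depends on an unstated weight

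*Protocol article*

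**What the plan says.** The Interim analysis section plans one look in each cohort, "when 50% of patients have been randomised and have completed 12 weeks of follow-up". It sets two numeric criteria on the posterior probability that the hazard ratio is below 1. Above 0.9 the trial stops for efficacy. For the other direction the text reads "Similarly, we would stop for futility if Pr (HR <1|data) < 0.1". Of both criteria it says that "efficacy and futility criteria will be based on the probability of treatment effects, given the observed data in our feasibility study". An independent data monitoring committee reviews the results and guides the decision.

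The feasibility study is described in the Background as single-arm with 32 patients: "The 28-day mortality was 3% and the 30-day readmission rate was 18.75"%. The Background adds that it used the APASL definition of ACLF, whereas the trial uses EF-CLIF. The Discussion repeats 32 patients, but the Sample size section gives 59. The Screening and randomisation section says that the statistician will be blinded to the feasibility results and to allocation in the trial.

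The Design section gives as the trial's purpose "to determine the efficacy and safety of the new model of care".

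**The concern.** Pr(HR<1) < 0.1 is the same statement as Pr(HR≥1) > 0.9. Although labelled futility, the bound therefore works as a harm signal, and the article states no other numeric criterion in that direction.

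The feasibility study has no control group and cannot supply a hazard ratio of its own. Its patients can be used in two ways: added to the LivR Well side, or set against a historical mortality rate. Both pull the posterior towards benefit. The lower bound then has to overcome that pull before it can register excess deaths in the randomised comparison, while the efficacy bound becomes easier to reach.

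Safety is a stated purpose of the trial and control mortality in the ACLF cohort is assumed to be about one in three. What is at stake is whether the one formal criterion put to the committee can show a rise in mortality.

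**Working it through.** **Inputs from the article.** The Sample size section plans "using a 2-sided alpha of 5%, a power of 80%, and an anticipated 20% dropout", and takes ACLF control mortality from a published cohort, "with a rate of 33.9% demonstrated in a study of 1343 hospitalised patients". The design mortality on LivR Well is 8.5%, with 60 per arm. Half of 60 gives 30 per arm at the look. Feasibility mortality of 3% in 32 patients is 1/32 = 3.1%, which fits the one death reported within 28 days (day 16).

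**The plan's own figure.** For 33.9% against 8.5%, the two-proportion formula gives 39.4, so 40 per arm. With continuity correction it gives 47. Then 47/0.8 = 58.75, so 59 per arm or 118 in total, against 120 stated. The sample size is reproduced closely enough to take 30 per arm as the interim size. The article states no operating characteristics for the interim rule, so there is none to reproduce.

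**Assumptions made here.** Death by day 28 stands in for the hazard ratio (under proportional hazards, HR<1 is equivalent to a lower death proportion). The priors are Jeffreys, Beta(0.5, 0.5), in each arm. The harm scenarios are assumed, not taken from the article. The feasibility data enter the LivR Well arm with weight w:

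- LivR Well: Beta(0.5 + x + w·1, 0.5 + 30 − x + w·31)
- Control: Beta(0.5 + y, 0.5 + 30 − y)

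Here x and y are the deaths in each arm. For every pair (x, y), Pr(p_LivR < p_control) is computed and compared with 0.1 and 0.9. The pairs are weighted by their binomial probabilities.

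**One data set as illustration.** Take 16/30 deaths on LivR Well and 10/30 on control. The posterior probability of benefit is 0.06 on randomised data alone, so the bound fires. It is 0.18 at w = 0.2, 0.41 at w = 0.5 and 0.72 at w = 1. At full weight the LivR Well arm becomes (16 + 1)/(30 + 32) = 17/62 = 27%, below the 33% on control.

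**Probability that each bound fires, 33.9% control against 50% LivR Well, 30 per arm**

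| Weight of feasibility data | Lower bound (<0.1) | Efficacy bound (>0.9) |
|---|---|---|
| None | 54% | 0.7% |
| 20% | 27% | 2.4% |
| Half | 9% | 9% |
| Full | 1.6% | 30% |

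**Sensitivity.**

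- *Flat priors:* 50%, 25%, 8% and 1.3% for the lower bound, in the same order.
- *60% mortality on LivR Well:* 81% with no borrowing, 53% at 20% weight, 22% at half weight and 5% at full weight.
- *Feasibility size of 59 (2 deaths), full weight:* below 1% at both 50% and 60% mortality.
- *24 per arm (20% lost), flat priors, 50% mortality:* 43% with no borrowing, 0.8% at full weight.
- *Assumed 10% control mortality:* at full weight 15% (LivR Well 20%) and 34% (LivR Well 30%), against 44% and 78% with no borrowing.
- *Log hazard ratio scale:* take a normal prior centred on ln(0.077), where 0.077 = ln(1 − 1/32)/ln(1 − 0.339), with variance 1 (one death). At a true HR of 2 there are about 27 events, so the variance of the estimate is 4/27.1 = 0.148. The bound fires in 29%, against 70% with a flat prior.
- *No true effect (33.9% in both arms):* 11% with no borrowing, 0.2% at full weight.

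**Passages side by side.** A statistician blinded to the feasibility results cannot compute a posterior that includes them. Adding them to one arm also requires knowing which arm is LivR Well. The interim rule and the blinding statement cannot both be followed as written unless someone else does the calculation, and the article names no one.

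**The case against.** The strongest reply is that the article fixes neither the form nor the weight of any prior, and that its two formulas condition simply on data. The reference to the feasibility study might be design rationale, and the blinding statement favours that reading. Prior details are also commonly left to the analysis plan. Part of this stands: no single firing probability can be attributed to the plan. However, the sentence places the feasibility data in the conditioning clause that defines both criteria. If rationale was meant, the wording misstates the rule. The point concerns what the article does say, not detail that it omits.

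A reader might infer that the lower bound almost never fires when LivR Well raises mortality. The documents do not support that without a condition. It is true at or near full weight with 33.9% control mortality. It is not true at 20% weight (27%), nor at 10% control mortality even with full weight (15% to 34%).

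A reader might also infer that the committee would have to let a harmful programme continue. That does not follow. The committee guides the decision, serious adverse events go to the ethics committee immediately, and the Data Availability section describes a safety board active throughout. None of these comes with a stated between-arm threshold, but each can lead to stopping.

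Finally, the Statistical analyses section says that "in-patients in the intervention arm may be discharged home earlier due to perceived safety with regular home visits". The article presents this as a source of bias and the reason for a subgroup analysis. It does not call it a route to harm, and this point does not depend on it.

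**Conclusion.** The concern holds in conditional form. The bound labelled futility is the only numeric criterion pointing towards harm, and the article bases it on favourable single-arm data collected under another ACLF definition. Borrowing lowered its chance of firing in every harm scenario computed. For 50% against 33.9% mortality, the loss runs from about half (54% to 27%, at 20% weight) to nearly all (54% to about 2%, at full weight). At full weight, the efficacy bound fires in about 30% of the same harmful trials, so stopping for apparent success is likelier than stopping for harm.

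These sizes rest on 30 per arm, day-28 death in place of the hazard ratio, Jeffreys priors and assumed harm scenarios. They apply to the ACLF cohort only. The direction also holds with flat priors, with the 2/59 figure and on the log hazard ratio scale. The conflict with the blinding statement and the 32 against 59 discrepancy need no assumptions.

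The documents do not support going further and calling the week-12 timing of the look an error, or the lack of a separate mortality stopping rule a defect of the design.

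**What to change.** In the Interim analysis section, state that the lower bound, Pr(HR<1|data) < 0.1, is computed from the randomised data only, and that crossing it signals likely harm as well as futility. The plan's threshold, committee and single look stay as they are. Reconcile the section with the blinding statement under Screening and randomisation. Reconcile the feasibility size of 32 (Background, Discussion) with 59 (Sample size).

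The cost is a wording change with no new data. The statistical price is that, with no true effect, the lower bound fires in about 11% of ACLF trials instead of about 0.2% under full-weight pooling. That is what the plan's own 0.1 threshold implies. Whether to add a separate mortality stopping rule or change the timing of the look is for the sponsor and the data monitoring committee to decide.
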